### Safety assessment

2.13

Safety will be assessed by observing and recording adverse events and conducting electrocardiogram (ECG) examination. Common adverse events associated with acupuncture therapy include bleeding, needle fainting, subcutaneous hematoma, and pain. The acupuncturist responsible for treatment needs to evaluate the severity of adverse events and promptly record and report the occurrence time, symptoms, duration, severity, treatment measures taken, and resolution time of such events. The grading for the severity of adverse events is categorized into three levels: grade 1 for mild, grade 2 for moderate, and grade 3 for severe or medically significance. Patients experiencing severe adverse events should stop acupuncture therapy, receive timely care, and the events must be reported to the Ethics Committee of Shanghai Putuo District Central Hospital within 24 h.

### Data management

2.14

The case report form of each patient will be timely filled out by an independent researcher, with all data accurately recorded. Patients’ medical histories, original data, and CRF tables will be stored in the clinical research office. Data will be entered into an EXCEL sheet using a double-entry method, followed by cross-check for data consistency. Any discrepancies found will require a recheck and correction of the abnormal values based on the CRF and original data. The identified database will be converted into the SPSS statistical software format and locked for data analysis by a qualified statistician.

### Measures to improve compliance

2.15

Patients will be followed up during the treatment course to closely monitor their compliance with the treatment.Patients in the sham acupuncture group will receive compensatory therapy after the observation period.

### Statistical analysis

2.16

All data will be analyzed using SPSS 27.0 statistical software. In accordance with the intention-to-treat (ITT) principle, patients who have received at least one treatment session will be included in the analysis. Basic information, baseline data, and efficacy evaluation will be analyzed using both the full analysis set (FAS) and per-protocol set (PPS). In case of inconsistent results between the two datasets, further analysis and evaluation will be conducted. Missing data will be imputed using multiple imputation method. For continuous outcomes, post-treatment data are presented as mean±SD if normally distributed with equal variances; otherwise, they are presented as median (IQR). ANCOVA will be used to adjust for baseline values and confounders (e.g., age, gender, revascularization therapy status), with adjusted mean differences and 95% CIs reported. For categorical data, frequencies and percentages will be presented, and potential confounders will be screened via univariate analysis before constructing stepwise logistic regression models to adjust for confounders and report odds ratios with 95% CIs, followed by validation of the model’s goodness of fit. Further, patients will be grouped based on infarction location to analyze EEG indicators in each subgroup. Receiver operating characteristic (ROC) curve analysis will be conducted to evaluate the predictive value of EEG as an efficacy indicator for acupuncture response, with the area under the curve (AUC) and 95% CI reported. For correlation analysis, Pearson correlation will be applied to normally distributed continuous data, while Spearman correlation will be used for ordinal data. All data analysis will be conducted using two-tailed tests with a significant level of 5%.

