### Randomization and allocation concealment

2.8

The grouping will be performed using a completely random method. The random allocation sequence will be generated through an online randomization tool Med Sci (http://tools.medsci.cn/rand) and managed by an independent researcher. Stroke patients who meet the inclusion criteria will be randomized into the acupuncture group or the sham acupuncture group in a 1:1 ratio after signing the informed consent. Cards printed with information on the allocated groups will be placed in opaque envelopes. Patients will receive envelopes sequentially according to the order of inclusion. An acupuncturist will open envelopes prior to treatment and conduct the corresponding treatment. The randomization process will be carried out by an independent researcher who is not involved in the recruitment, evaluation, and intervention.

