### Blinding

2.9

This study will employ blinding in efficacy assessment and statistical analysis. Since sham acupuncture will be used as the control, it is difficult to blind participants and acupuncturists. Additionally, the grouping information will be blinded to efficacy assessors and statistical analysts. Acupuncturists will administer acupuncture therapy in accordance with the treatment plans corresponding to the random numbers. Patients will be separated to prevent communication. Researchers responsible for scale evaluation and EEG analysis will not participate in the grouping or intervention processes. Besides, statistical analyst will not be involved in the implementation of the study to avoid selective bias produced by objective factors.

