### Basic information collection

2.11

Basic demographic and medical history data from eligible patients will be collected using a self-designed questionnaire, including gender, age, education, marital status, residence, occupation, as well as smoking/alcohol use, family stroke history, underlying diseases, and medication history. Basic information and baseline assessments will be recorded and gathered post random grouping.

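### The analysis labelled ITT admits only patients with at least one session, a modified ITT set that can bias the comparison because starting treatment may depend on the arm

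*Protocol article*

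**What the plan says.** Section 2.16 (Statistical analysis) sets the rule for the analysis population: "In accordance with the intention-to-treat (ITT) principle, patients who have received at least one treatment session will be included in the analysis". It then says that "efficacy evaluation will be analyzed using both the full analysis set (FAS) and per-protocol set (PPS"), and on incomplete data only that "Missing data will be imputed using multiple imputation method". The article names no other efficacy set and does not define the two it names any further.

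Three other sections bear on whether a patient's start of treatment can depend on the arm:

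- Section 2.8: "Patients will receive envelopes sequentially according to the order of inclusion", and "An acupuncturist will open envelopes prior to treatment and conduct the corresponding treatment".
- Section 2.9: "Since sham acupuncture will be used as the control, it is difficult to blind participants and acupuncturists". The third limitation in the Discussion repeats this. Only assessors and statistical analysts are to be blinded.
- Section 2.11: "Basic information and baseline assessments will be recorded and gathered post random grouping", so some time passes between allocation and the first session.

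**The concern.** The label and the rule do not match. Intention-to-treat means every randomised patient, analysed in the allocated arm. A rule that requires one session drops anyone randomised but never treated, and that is an exclusion made after randomisation.

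Such an exclusion is commonly accepted where nobody involved in starting treatment knows the arm, since the losses are then unrelated to allocation. This trial cannot use that argument. The person who gives session 1 has already opened the envelope, and session 1 is the event that decides entry to the analysis. If patients who fail to start differ in prognosis, and do so more in one arm, the primary comparison on the simplified Fugl-Meyer change is no longer between the groups that were randomised. The direction could favour either arm, and the ITT label would hide the problem from readers of the results.

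**Working it through.** **Inputs.** From section 2.7: SD 7.81, planned difference 6.59, power 0.9, 30 per group before dropout, 15% dropout, 70 in total. With 1:1 allocation this is 35 per arm. From section 2.16: two-sided 5% level. The number leaving before session 1 (k) and how far they differ (g) are not in the documents, so both are assumptions here.

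**The plan's own figure.** n = 2 × (1.960 + 1.282)² × 7.81² / 6.59² = 29.5, so 30 per group, as stated. For dropout, 60/0.85 = 70.6, close to the stated 70. The sample size is not in question.

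**Shift in the estimate.** Suppose all k leavers are in one arm and their mean outcome differs by g from those who stay. The mean of the stayers then differs from the mean of the full arm by k × g / 35. With g = 1 SD = 7.81:

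| k of 35 | Shift (points) | % of 6.59 | Two-sided type I error |
|---|---|---|---|
| 0 | 0 | 0 | 5.0% |
| 1 | 1 × 7.81/35 = 0.22 | 3% | 5.2% |
| 2 | 2 × 7.81/35 = 0.45 | 7% | 5.6% |
| 3 | 3 × 7.81/35 = 0.67 | 10% | about 6.5% |
| 5 | 5 × 7.81/35 = 1.12 | 17% | about 9% |

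At g = 0.5 SD each shift is half as large: 0.11, 0.22, 0.33 and 0.56 points for k = 1, 2, 3 and 5.

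**Type I error.** With 35 per arm, SE = 7.81 × √(2/35) = 1.867. The error is Φ(−1.96 + shift/SE) + Φ(−1.96 − shift/SE). For k=3, shift/SE = 0.669/1.867 = 0.358, which gives Φ(−1.602) + Φ(−2.318) = 0.065. For k=5 it is 1.116/1.867 = 0.598, which gives about 0.09. Using the reduced arm size in the SE, 7.81 × √(1/35 + 1/(35−k)), gives 6.4% and 8.9%, so the choice is immaterial.

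**Role of the planned ANCOVA.** Section 2.16 adjusts for baseline and confounders. The shifts above therefore apply only to the part of the leavers' difference that those covariates do not explain. In a simulation with 35 per arm and an assumed baseline–outcome correlation of 0.7, leavers who differed only through baseline left the treated-only and all-randomised ANCOVA estimates almost equal: 0.01 against 0.00 for 3 leavers, and 0.04 against 0.04 for 5.

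**Would imputation alone repair it?** In the same setting, but with a 1 SD difference that baseline does not explain:

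| Leavers | Treated-only ANCOVA | All randomised, outcomes imputed | All randomised, true outcomes observed |
|---|---|---|---|
| 3 | 0.04 | 0.04 | 0.72 |
| 5 | 0.03 | 0.03 | 1.15 |

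Imputing untreated patients from baseline and arm gives the same answer as leaving them out. The gap to the analysis with observed outcomes (0.72 − 0.04 = 0.68; 1.15 − 0.03 = 1.12) matches the formula. Only observed Day 15 values close it.

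**The case against.** A good case can be made that the harm is small or absent.

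- **Knowledge of the arm.** A reader might infer that patients learn their arm and then leave. The documents do not say so. The envelopes are opaque, the acupuncturist opens them, both groups have rubber pads, the sham is meant to imitate real needling, and patients are kept apart. That "it is difficult to blind participants and acupuncturists" is an admission of difficulty and does not mean that patients are told. This stands, and it limits the claim about patients. It does not remove the route through the acupuncturist, who does know the arm and delivers the session that decides inclusion.
- **Few will leave.** Baseline is Day −1 to 0 and treatment starts on Day 1, so the interval is short. Patients must be clinically stable, severe needle phobia is excluded, and sham patients are offered acupuncture afterwards. This stands too: one or two leavers matter little. Five of 35 would put about the whole 15% dropout allowance into one arm before treatment begins.
- **The figures are a worst case.** They put all leavers in one arm, differing in one direction, with nothing explained by the covariates. That is correct, and they should be read as conditional.
- **The sets may be defined elsewhere.** Detailed definitions of the FAS and PPS may well be in a fuller document, and for that reason the point does not rest on how narrow the PPS is. But the article does state the one-session rule and attaches the ITT label to it, and nothing in it brings untreated patients back.

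**Conclusion.** The point holds as a should-fix. The population in section 2.16 is a modified ITT set under an ITT label, and the usual justification for such a set is not available when the treating acupuncturist knows the arm before session 1. The possible bias runs from nil, if everyone randomised starts treatment, to about 1.1 points (17% of the planned difference, type I error about 9%) if five in one arm leave untreated and differ by 1 SD unexplained by baseline. One or two such patients would shift the estimate by 0.22 to 0.45 points, with type I error of 5.2% to 5.6%.

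Two stronger readings are not supported. One is that the comparison is bound to be biased: the documents give no count of untreated patients and do not show that any will occur. The other is that rewording the set and relying on the planned imputation would cure the problem: without observed outcomes the estimate hardly moves.

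**What to change.** In section 2.16:

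1. Define the primary ITT/full analysis set as all randomised patients in the arm allocated, whether or not any session was received.
2. State that the Day 15 assessment will be sought from every randomised patient who has not withdrawn consent, including those never treated.
3. Use the planned multiple imputation only for values still missing, with a sensitivity analysis for departures from its assumption.
4. Keep the at-least-one-session set under its proper name, as a modified ITT sensitivity analysis and as the safety set.

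The cost is a few sentences, plus some effort to bring untreated patients back for Day 15. The required sample size stays at 30 per group and 70 in total. The small downside is that a few imputed or untreated outcomes enter the primary analysis. The trial is still recruiting, so the change can be made before the database is locked.

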### Inclusion criteria

2.4

Patients who meet diagnostic criteria of Western medicine for ischemic stroke, combined with CT or MRI;Patients who meet diagnostic criteria for phlegm and blood stasis obstructing meridians in TCM syndrome;Aged between 30 and 80, inclusive;First occurrence, or those with a previous stroke but without sequelae;1 week to 3 months after the onset of stroke;Lesion in one cerebral hemisphere with unilateral hemiplegia, Brunnstrom stage II-IV;Right handedness;Patients with clear minds, clinically stable conditions, and limb dysfunction caused by stroke.

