#### Primary outcome

2.12.1

The primary outcome is the change in limb motor function in stroke patients before and after treatment, assessed using the simplified Fugl-Meyer Assessment (FMA) scale. Limb motor function impairment will be quantified by evaluating upper/lower extremity functions, balance, sensation, and joint range of motion. The scale comprises 50 items (33 for upper limbs, 17 for lower limbs), with higher scores indicating better functional activity.

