##### Muscle tone

2.12.2.3

Limb muscle spasticity will be evaluated using the Modified Ashworth Scale (MAS) by assessing the resistance encountered during passive muscle stretching. The scale has 6 levels, ranging from no increase in muscle tone to rigidity. Level 0 indicates normal joint mobility, while level 4 indicates the most severe spasticity, with the joint immovable.

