## Discussion

3

Since ischemic stroke poses a severe threat to health, thrombolysis and thrombectomy after acute stroke can effectively reduce stroke-related mortality and disability rates (30). However, the strict time window for these treatments limits stroke patients’ therapeutic benefits (31). Most patients experience varying degrees of neurological deficits after acute stroke, with approximately 50–80% developing limb motor dysfunction related to ischemic lesion during recovery period, which indicates a significant demand for post-stroke functional rehabilitation (32). The Stroke Roundtable Consortium defines the first 24 h post-stroke as the hyperacute phase, the first 7 days as the acute phase, the first 3 months as the early sub-acute phase, 4–6 months as the late sub-acute phase, and beyond 6 months as the chronic phase (33). In the early post-stroke period, a series of neuronal plasticity-enhanced mechanisms trigger dendritic growth, axon sprouting, and the formation of new synapses (34). The “proportional recovery rule” suggests that patients can recover approximately 70% of lost function within 3–6 months post stroke (35), though this proportion varies with individual differences, lesion location and severity, as well as the effectiveness of rehabilitation measures. Therefore, seizing the critical time window for post-stroke rehabilitation and implementing effective rehabilitation measures are crucial for restoring impaired neural functions, improving disease prognosis, and enhancing patients’ quality of life.

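### Categorical outcomes: univariate screening plus stepwise logistic regression should be replaced by one pre-specified model that always contains treatment (minor, free improvement)

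*Protocol article*

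**What the plan says.** Section 2.16 (Statistical analysis) sets two routes.

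- **Continuous outcomes:** "ANCOVA will be used to adjust for baseline values and confounders (e.g., age, gender, revascularization therapy status), with adjusted mean differences and 95% CIs reported". This covers the primary outcome, since section 2.12.1 states: "The primary outcome is the change in limb motor function in stroke patients before and after treatment", measured on the simplified Fugl-Meyer scale.
- **Categorical data:** frequencies and percentages, after which "potential confounders will be screened via univariate analysis before constructing stepwise logistic regression models to adjust for confounders", odds ratios with 95% confidence intervals are reported, and goodness of fit is checked. No candidate list and no entry or removal threshold is given, and nothing says that treatment stays in the model.

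No binary efficacy endpoint is defined. The nearest to a categorical outcome is the secondary Modified Ashworth Scale (MAS) in section 2.12.2.3: "The scale has 6 levels, ranging from no increase in muscle tone to rigidity".

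Three other statements bear on the covariates. Entry is allowed at "1 week to 3 months after the onset of stroke" (section 2.4). Section 2.8 says "The grouping will be performed using a completely random method", with no stratification named. The Discussion cites a rule that "patients can recover approximately 70% of lost function within 3–6 months post stroke".

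**The concern.** After randomisation, baseline differences between the arms arise by chance. Choosing confounders by their p-values in the trial's own data therefore answers a question the design has already settled. Covariates earn a place in the model because they predict the outcome, and that can be decided beforehand.

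At this sample size, which covariates survive screening and stepwise removal depends heavily on the sample, so the reported odds ratio comes from a model nobody specified. Confidence intervals from the final model also ignore the selection step. If the treatment term is a candidate like any other, it can be removed, or reported mainly when its estimate happens to be large.

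This is a method the article positively states, not a detail left open. A later analysis plan would have to overrule the sentence rather than complete it.

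A lesser matter concerns the ANCOVA. Time since stroke is not among the example covariates, although entry spans most of the early recovery period and the outcome is a two-week change.

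**Working it through.** **1. The plan's own figure.** Inputs from section 2.7: SD 7.81, difference 6.59, alpha 0.05 (two-sided per section 2.16), power 0.90.

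n per arm = 2 × (1.960 + 1.282)² × 7.81² / 6.59² = 29.5, rounded up to 30. Then 30 × 1.15 = 34.5, rounded up to 35 per arm, or 70 in total. The stated sample size reproduces and does not depend on this point.

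**2. Stepwise selection.** Assumptions, none of them from the documents: binary outcome, 60 patients, 8 independent candidate covariates, p < 0.10 to pass the univariate screen and p < 0.10 to stay in backward removal. Either none or three of the covariates are prognostic. There are 3,000 simulated trials per setting. The fixed comparison model holds treatment and three pre-specified covariates (the prognostic ones where there are any).

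| Quantity | No covariate prognostic | Three prognostic |
|---|---|---|
| Distinct final models, true OR 1 / 3 | 90 / 107 | 144 / 168 |
| Share of most frequent model, true OR 1 / 3 | 40% / 36% | 10% / 7% |
| Treatment lost if selectable, true OR 3 | 36% | 48% |
| Median OR when treatment kept, true OR 3 | 4.17 | 4.73 |
| Median OR in fixed model, true OR 3 | 3.31 | 3.35 |
| Type I error, treatment forced in | 6.0% | 5.6% |
| Type I error, fixed model | 6.0% | 5.1% |

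The first four rows treat treatment as one of the selectable terms. With treatment forced in, power at a true OR of 3 was 55.5% and 48.3%, against 54.6% and 49.4% for the fixed model, so little changes.

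**3. Time since stroke in the ANCOVA.** The documents give no correlation between time since stroke and the outcome, so the partial correlation r is assumed. Taking 7.81 as the SD before this covariate is added, residual SD = 7.81 × √(1 − r²), and power = Φ(6.59 / (SD × √(2/30)) − 1.96) at 30 per arm.

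| r | Residual SD | Power | 95% CI half-width | n per arm for 90% |
|---|---|---|---|---|
| 0 | 7.81 | 90.5% | 3.95 | 30 |
| 0.1 | 7.77 | 90.7% | 3.93 | 30 |
| 0.3 | 7.45 | 92.9% | 3.77 | 27 |
| 0.5 | 6.76 | 96.5% | 3.42 | 23 |

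How large is r likely to be once baseline is in the model? Suppose recovery is exponential, reaching 70% of an onset deficit D with time constant τ. With C the full score, the score at time t is S = C − 0.3D − 0.7D·exp(−t/τ). The next 14 days bring a gain of 0.7D·exp(−t/τ)·(1 − exp(−14/τ)) = (1 − exp(−14/τ))·(C − 0.3D − S).

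For a fixed D the gain is an exact linear function of the baseline score, so time adds nothing. Letting D vary, with entry uniform over days 7–90 and τ of 20–60 days, the partial R² of log time was 0.2–0.9% for D of 40–60 and 0.5–4.6% for D of 20–80. Power rose by at most about 1 point. A baseline measured with error would leave time somewhat more to explain.

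**The case against.** The best defence is that the sentence builds stepwise models in order to adjust for confounders. Its natural reading is that confounders are selected around a treatment term that stays. On that reading type I error is near nominal and power is almost that of a fixed model. This stands as a limit on the harm: the lost treatment terms and exaggerated odds ratios belong to a reading that the text permits but does not state. It does not rescue the method, because the model is still chosen by the data and gains nothing over a fixed one.

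It is also fair that no binary efficacy endpoint exists and that the MAS is ordinal and secondary. The simulated odds ratios therefore illustrate the method and do not describe a named outcome.

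Three stronger readings are tempting and are not supported.

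- **That stepwise selection compromises the primary result.** It does not. Change in Fugl-Meyer score is continuous and goes to ANCOVA.
- **That the ANCOVA leaves out time since stroke and so loses precision.** The covariates are given as examples, so time is unnamed rather than excluded. Closing such a list is commonly left to an analysis plan, which is not shown here. Baseline adjustment, already planned, may capture most of what time would explain. Nor does the Discussion rank time first: it attributes variation in recovery to individual differences, lesion location and severity, and rehabilitation.
- **That the trial is underpowered because of this.** The sample size reproduces from its own inputs.

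**Conclusion.** The point holds as a minor one. For categorical data the article prescribes a method ill-suited to a small randomised trial and does not protect the treatment term. The main consequence is instability: with 60 patients and 8 candidates, the most frequent final model appeared in only 7–10% of simulated trials when three covariates mattered. A seriously distorted odds ratio arises only if treatment is itself open to removal. These figures rest on assumed thresholds, candidate numbers and a binary outcome.

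Naming time since stroke in the ANCOVA is worthwhile but secondary. Its value runs from negligible (90.7% power at r = 0.1) to material (96.5% at r = 0.5). The documents do not say where in that range it lies, and the recovery-curve check points to the low end once baseline is adjusted for.

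**What to change.** In section 2.16, delete the univariate screening and stepwise selection. State instead that each categorical outcome is analysed with one pre-specified model that always includes treatment and a fixed covariate set: proportional odds for the MAS, and logistic regression for any binary outcome that is later defined. Refer to prognostic covariates rather than confounders.

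In the same edit, name time from onset to randomisation as a fixed covariate beside the baseline value in the ANCOVA, and add it to the baseline items in section 2.11. Eligibility already requires it, so it needs no new data collection.

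The cost is protocol or analysis-plan wording only, with no change to sample size or conduct. The trial is recruiting (section 4), so the change should be made and dated before the data are unblinded.

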### Sample size calculation

2.7

Sample size for this study is estimated according to the formula for the comparison of means in a randomized controlled trial. Referring to the relevant literatures (26, 27), we estimate the pooled standard deviation (*σ*) of the treatment group and the control group to be 7.81, and the difference between the means of the two groups (*δ*) to be 6.59. We set the significant level (*α*) at 0.05, the Type II error rate (*β*) at 0.1, and the statistical power (1-β) at 0.9. After substituting the values into the formula, calculated sample size per group requires 30 cases. Considering a 15% dropout rate, a total of 70 cases will be enrolled.

$$n=\frac{2{\left(z_{\alpha }+z_{\beta }\right)}^{2}*\sigma^{2}}{\delta^{2}}$$

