
There are still some limitations in the design of this study: (1) the study does not restrict the infarction sites of included patients to the same hemisphere or specific locations, leading to increased heterogeneity in EEG signals; (2) the study duration is short, and there is a lack of follow-up observation after treatment course, making it difficult to ascertain the long-term efficacy of acupuncture therapy; (3) due to the treatment characteristics of acupuncture, it is challenging to implement blinding for acupuncturists and patients; (4) a multicenter study is not designed, making it impossible to verify the general applicability of the study across different populations and medical conditions. Hence, based on this study, we will further conduct multicenter, large-sample, long-term follow-up clinical trials for ischemic stroke patients in recovery stage.

Collectively, the primary objective of this clinical trial is to evaluate the efficacy and safety of the “simultaneous treatment of phlegm and blood stasis” acupuncture therapy in improving limb motor impairment in ischemic stroke patients with hemiplegia using functional scales, while exploring its underlying electrophysiological mechanisms through EEG. By conducting this clinical study, we expect to provide reliable scientific evidence for the clinical application of acupuncture therapy featuring characteristic acupoint combinations based on TCM syndrome differentiation in the field of neurological rehabilitation for ischemic stroke.

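### EEG indicators are to be analysed within each infarct-location subgroup, but no test is named of whether the acupuncture effect differs by location

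*Protocol article*

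**What the plan says.** After setting out baseline-adjusted ANCOVA for continuous outcomes, section 2.16 (Statistical analysis) adds that "patients will be grouped based on infarction location to analyze EEG indicators in each subgroup". The section closes with a blanket rule: "All data analysis will be conducted using two-tailed tests with a significant level of 5" per cent. It names no arm-by-location interaction.

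The limitations paragraph of the Discussion gives the background: "the study does not restrict the infarction sites of included patients to the same hemisphere or specific locations, leading to increased heterogeneity in EEG signals".

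Section 2.12.2.8 (Coherence analysis) compares coherence between the two arms by t-test or Wilcoxon test. It mirrors the recordings of right-sided infarcts so that both lesion sides can be analysed together, and it applies a Bonferroni correction. That correction appears only there. Nothing ties it to the location subgroups or to the other EEG indicators.

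Section 2.7 sizes the trial for one overall comparison on the Fugl-Meyer score. Section 2.8 describes simple randomisation and mentions no stratification by infarct site.

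**The concern.** Separate results in separate subgroups do not answer whether the effect differs between them. A significant result in one location beside a non-significant one in another is what a uniform effect often produces when each part is small. Here the parts are small, and their sizes and arm balance are left to chance, because infarct site is neither restricted nor stratified.

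EEG is in the trial's title, stands among the secondary outcomes and supports the aims on mechanism and biomarkers. A reader shown location-by-location results at the 5% level could conclude that acupuncture changes cortical activity for some infarct sites and not for others, when the data do not distinguish the two cases.

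**Working it through.** **Inputs from the plan (section 2.7).** The SD is 7.81 and the expected gap between the arms is 6.59. Two-sided alpha is 0.05 and power is 0.9.

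**Reproducing the plan's figure.** n per arm = 2 × (1.960 + 1.282)² × 7.81² / 6.59² = 29.5, rounded up to 30. This agrees with "calculated sample size per group requires 30 cases". With 70 enrolled and 15% dropout, 70 × 0.85 = 59.5, so about 60 completers. The standardised planning effect is 6.59 / 7.81 = 0.844 SD. At 30 per arm the two-sample t-test has 89% power for it.

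**Assumptions not in the plan.** There are k = 2, 3 or 4 locations of equal size, one EEG indicator, 60 evaluable patients and the same true effect in every location. The EEG effect size is unknown, so three values are shown. The largest is the Fugl-Meyer planning value, used only as an illustration.

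**Formulas.** Patients per arm per location = 30 / k, that is 15, 10 and 7.5 (the last is notional). Let p be the noncentral-t power in one location at two-sided 5%.
- Mixed verdict (some locations significant, some not): 1 − p^k − (1 − p)^k
- At least one false positive when there is no effect: 1 − 0.95^k

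| Uniform effect | Quantity | k = 2 | k = 3 | k = 4 |
|---|---|---|---|---|
| 0.844 SD | power p | 0.607 | 0.431 | 0.328 |
| | mixed | 48% | 74% | 78% |
| 0.5 SD | power p | 0.262 | 0.185 | 0.146 |
| | mixed | 39% | 45% | 47% |
| 0.3 SD | power p | 0.125 | 0.097 | 0.084 |
| | mixed | 22% | 26% | 30% |
| none | any false positive | 9.8% | 14.3% | 18.5% |

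Example for k = 2 at 0.844 SD: 1 − 0.607² − 0.393² = 1 − 0.368 − 0.154 = 0.477.

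**Sensitivity at 0.844 SD.** Two locations split 70/30 give powers of 0.761 and 0.391, so the mixed rate is 0.761 × 0.609 + 0.391 × 0.239 = 56%. With all 70 patients evaluable, two equal locations give 44%.

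**The alternative.** In 40,000 simulated trials per setting with 60 patients, a single arm-by-location F test gave a false location difference in 4.8-5.1% of trials. That held for 2, 3 and 5 locations, and both with no effect and with a uniform effect of 0.844 SD.

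**Its limit.** With two equal locations, the difference between the two location-specific effects has variance 2 × (2σ²/15) = 4σ²/15. The overall effect has variance 2σ²/30 = σ²/15. The standard error is therefore doubled, so power to detect a real difference between locations is low.

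**The case against.** **The split is supplementary.** A reader might infer that subgrouping throws away the full sample's power for EEG. The documents do not support that. The sentence is introduced as a further step, section 2.12.2.8 makes a pooled two-arm coherence comparison, and section 2.16 plans ANCOVA for continuous outcomes. The covariate list there is given as examples, so location is not ruled out as an adjustment.

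**The faulty inference is not written down.** A reader might also infer that the plan intends to claim location-specific effects. It does not say so, nor does it spell out a between-arm test in each subgroup. The step could be read as description in response to the acknowledged heterogeneity. This stands as a limit on the point. Even so, the two-arm comparison in section 2.12.2.8 and the blanket 5% rule make within-subgroup testing the natural reading, and nothing labels the analysis descriptive or exploratory.

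**Bonferroni is planned.** It is stated for coherence only. Extending it to the subgroups would lower the false-positive rate but also the power in each, and it still would not test a difference between locations.

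**Detail may sit in the analysis plan.** Subgroup definitions and reporting format may well be there, and their absence is not held against the article. The point concerns the method that the article does state.

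**The rates rest on assumptions.** This is correct. The higher figures depend on a Fugl-Meyer effect size borrowed for EEG, and the number and size of locations are assumed.

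**Conclusion.** The point holds as a modest, inexpensive improvement to a secondary analysis. The stated step cannot show whether the effect differs by location. If arms are tested within subgroups, apparent differences will arise from a uniform effect in roughly a fifth to three quarters of trials (22-78%), depending on effect size (0.3 to 0.84 SD) and number of locations (2 to 4). With no effect, 10-19% of trials show at least one falsely significant location per indicator. These figures assume 60 completers, equal subgroups and uncorrected two-sided 5% tests. The direction of the conclusion does not depend on the exact values, but the size does. The primary Fugl-Meyer comparison and the full-sample EEG comparison stand as planned.

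**What to change.** For each EEG indicator, fit one ANCOVA on all patients: post-treatment value on arm, baseline EEG value, infarct location and arm by location, with the location categories named before analysis. Base any statement of a location-specific effect on the interaction term. Report location-specific estimates with 95% CIs as exploratory description, without significance claims inside subgroups.

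State that the interaction test has low power at this sample size, so a non-significant result does not show that effects are equal.

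The cost is some wording and slightly more modelling. Section 2.16 already plans baseline-adjusted ANCOVA, and no patients, visits or measurements are added. The trial is still recruiting, so the change can be made before any analysis.
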